**Rationale & background information**

## Back Packs are the most common method of transporting external cargo, with 90% of students using a traditional BP. In most studies, the weight recommendations range from 10-15% of children’s body mass ^3,4^. Observed postural changes in both static stance and dynamic gait, have been reported with external loads greater than 20% of a child’s body mass ^5^. Larger loads have been related to back pain in children^6^. Previous studies cite that between 4.7 % and 38.0% of children carry loads greater than 20% of their body weight daily ^3,7^. Two-thirds of children affirm the daily use of BPs when walking an average of 14.55 km to and from school each week ^8^.

References

**Study goals and objectives**

## The purpose of this study is to analyze the changes of the spatio-temporal parameters of gait, in school children, with five specific load conditions in a typical BP because we can detect which it is the limit weight in the BPs in the kids to go to the school without change in their gait .

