**Methodology**

### *Procedure*

### Two examiners will be responsible for the system software and collecting data. General information, including height and weight, will be recorded. To measure gait parameters, the protocol use for the Optogait reliability testing will be used^17^. This involved the children walking on a walkway at a comfortable speed, repeating this walk three times and calculating the mean speed. Prior to data collection, the children performed one familiarization trial for five minutes. Children will be asked to walk naturally, facing forward, with their hands out of pockets; wearing light, comfortable clothes, with the BP placed correctly. As the children start walking, the researchers selected the foot of the first step inside the bars, in the Optogait software. After being instructed to ‘*walk slowly at a comfortable speed’*, the children walk from a point two metres in front of the bar and stopp at a point two metres behind the last bar, to minimize effects of acceleration and deceleration . After this, they will be instructed to turn around and walk back to the starting point.. Only steps in the sensor areas will be included in the analysis. Recording six to eight strides is reported as sufficient to obtain representative data for unimpaired adults (defined as 95% confidence intervals within 5% of error)^27^. Subsequently, five experimental conditions will be measured: without BP, BP loads of 5%, 10%, 15%, and 20% of body weight. The order of these loaded conditions was random.

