**Data Management and Statistical Analysis**

### SPSS v. 25.0 program (IBM Inc., USA) will used for statistical calculations using descriptive and inferential statistical tests. The gait data will be tested for normality by using the Kolmogorov–Smirnov test, set at a significance level of p < 0.05. To determine test-retest reproducibility, one-way ANOVA Intraclass Correlation Coefficients (ICC) with the 95% Confidence Interval (95%CI) will be conducted in a sample of 25 children.

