### The spatio-temporal gait parameters measured will be step length, stride length, single limb support time, double limb support time, swing and stance phase times. Averaged values for continuous variables with non-normal distribution will be expressed as Mean ± Standard deviation (SD). The one-way analysis of variance (ANOVA) will be performed to compare the groups with Bonferroni post-hoc test, will be performed to determine the effect of different weights.

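### The stated aim is the heaviest load without gait change, but the only analysis of load is a test for difference, so any limit drawn from it would depend on the number of children

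*Protocol*

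**What the plan says.** The Protocol, Study goals and objectives, describes a study of gait parameters under five load conditions and gives as its reason that the study can "detect which it is the limit weight in the BPs in the kids to go to the school without change in their gait".

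Under Methodology, "five experimental conditions will be measured: without BP, BP loads of 5%, 10%, 15%, and 20% of body weight".

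Under Data Management and Statistical Analysis, the outcomes are "step length, stride length, single limb support time, double limb support time, swing and stance phase times". The analysis of load is given in one sentence: "The one-way analysis of variance (ANOVA) will be performed to compare the groups with Bonferroni post-hoc test", which "will be performed to determine the effect of different weights". The same section also plans descriptive statistics, a normality test and a test-retest ICC in 25 children. None of these is tied to the limit. A significance level is given for the normality test only ("set at a significance level of p < 0.05").

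The protocol gives no number of children for the load comparison. It also does not say how the ANOVA result becomes a limit.

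**The concern.** The objective asks for a positive statement that gait is unchanged up to some load. The analysis can only provide evidence that gait has changed. A post-hoc p-value above the threshold does not show that a change is absent or small. It shows only that the study could not separate the change from zero.

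If the limit is taken as the heaviest load before the first significant contrast with no backpack, two things go wrong. In a small or noisy study, real changes go undetected and the limit drifts upwards. In a very large study, trivial changes become significant and the limit drifts downwards. The main practical result, a backpack weight for schoolchildren, would then reflect the number measured as much as their gait.

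**Working it through.** **No plan figure to reproduce.** The protocol states no sample size, power, SD or margin for the load comparison, so the numbers below are illustrations.

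**Inputs**
- From the protocol: five conditions (0, 5, 10, 15 and 20% of body weight), hence 5×4/2 = 10 pairwise contrasts, of which 4 are against no backpack; six gait parameters; a Bonferroni post-hoc test.
- Assumed: overall two-sided alpha 0.05 for the ANOVA, so 0.05/10 = 0.005 per pair; the numbers of children; the true changes, expressed as d, the mean within-child change divided by the SD of the within-child differences; and a paired analysis, which suits children measured under every load.

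**Step 1: chance of missing a real change, one contrast on one parameter.** Power comes from the noncentral t distribution with n−1 degrees of freedom and noncentrality d√n. The miss probability is 1 − power. For example, at n = 25 and d = 0.5 the noncentrality is 0.5×5 = 2.5, power is 30.5% and the miss probability 69.5%.

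| True change d | n = 25 | n = 50 | n = 100 |
|---|---|---|---|
| 0.5 | 69.5% | 27.9% | 1.8% |
| 0.3 | 92.3% | 77.9% | 44.7% |

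The pattern does not depend on counting all 10 pairs. With only the four contrasts against no backpack (0.05/4 = 0.0125), the misses are 56%, 18% and 1% for d = 0.5, and 86%, 67% and 32% for d = 0.3.

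**Step 2: smallest observed change that reaches significance.** This is t(1 − 0.005/2, n−1)/√n, in SDs of the difference: 0.62 at 25 children, 0.42 at 50, 0.29 at 100, 0.20 at 200, 0.14 at 400 and 0.10 at 800. Anything smaller would be classed as unchanged, so the study's size sets the effective definition of no change.

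**Step 3: same gait, different limit.** Suppose the true change is d = 0.1 for each 5% of load, so 0.1, 0.2, 0.3 and 0.4. The power to flag each load at 0.005 is:

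| Children | 5% | 10% | 15% | 20% | Load just below the first one flagged |
|---|---|---|---|---|---|
| 25 | 1% | 3% | 8% | 17% | usually none flagged, so 20% |
| 100 | 3% | 20% | 55% | 87% | about 10% |
| 200 | 8% | 50% | 92% | 100% | 5% or 10% |
| 400 | 21% | 88% | 100% | 100% | about 5% |
| 800 | 51% | 100% | 100% | 100% | 5% or none |

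The true gait response is the same in every row. Only the number of children differs.

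**Step 4: what a direct test of no change would need.** For one load and one parameter, a true change of zero, a margin m in SDs of the difference, 80% power and a 90% CI rule, n = ((1.645 + 1.282)/m)², or about 8.56/m². This gives 215 children for m = 0.2, 96 for 0.3, 54 for 0.4 and 35 for 0.5. The margins are assumed, because the protocol gives none.

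**The case against.** **The misreading is inferred.** A reader might infer that the protocol commits itself to treating non-significance as no change. It does not say so. The first part of the stated purpose, studying how gait changes across loads, is well served by difference tests, and the limit appears only in the clause giving the reason. This stands as a limit on the wording. But no other route from the analysis to a limit is offered, and the mismatch lies between two things the protocol states.

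**A SAP could supply a margin or decision rule.** That is true, and their absence alone would not be a finding. Still, a SAP that carried out the stated ANOVA faithfully could not answer the stated objective.

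**The miss probabilities are not the chance that a load is declared unchanged.** This stands. They cover one contrast on one of six parameters. If a change in any parameter counted, all six would have to be missed. With equal effects of 0.5 SD and independence, that is 0.695⁶ = 11% at 25 children and 0.279⁶ = about 0.05% at 50. The parameters are likely to be correlated, so the true figure would lie between these and the single-parameter values.

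**It is tempting to add that the one-way ANOVA makes the misses worse.** That is conditional. At 25 children and 0.5 SD, an analysis treating conditions as independent groups misses more only when the within-child correlation exceeds about 0.13. At zero correlation it misses slightly less (63.6%). The condition is likely to be met in repeated measures, but the protocol gives no correlation.

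**A reader might infer that the error always favours heavier loads, or that a null result at 20% would be reported as a 20% limit.** Neither is supported. A very large study errs the other way. The Rationale says postural changes, including in gait, "have been reported with external loads greater than 20% of a child" and no load above 20% is tested, but it also cites recommendations of 10-15%, inside the tested range. The protocol does not say how a null result at 20% would be reported.

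**Conclusion.** The objective and the analysis do not match. A limit "without change in their gait" cannot be established by ANOVA with post-hoc difference tests. If one is read from the non-significant contrasts, the only route this analysis offers, it moves with the number of children: too high in a small study, too low in a very large one.

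The direction of this dependence holds for any non-zero true change. Its size is illustrative only. For a single contrast on a single parameter, a 0.5 SD change is missed 69.5%, 27.9% and 1.8% of the time at 25, 50 and 100 children, and a 0.3 SD change 92.3%, 77.9% and 44.7%. These figures assume the effect size, the number of children, an overall alpha of 0.05 and a paired test. They do not give the probability of a wrong limit over all six parameters, which cannot be calculated without a rule for combining them.

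**What to change.** Change Study goals and objectives and the load paragraph of Data Management and Statistical Analysis together.

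1. Estimate the within-child difference from no backpack at each load, with confidence intervals. State that a non-significant test will not be taken as no change.
2. If a limit is to be declared, name in advance the deciding gait parameter or parameters and a margin that the sponsor justifies for children, for example against the test-retest error from the 25-child sample. The 5% figure under Methodology should not be borrowed: it describes stride-count precision in unimpaired adults.
3. Require the 90% CI of the within-child difference to lie wholly inside that margin. Test 5%, 10%, 15% and 20% in that order and stop at the first failure. The limit is the last load that passes.
4. If all loads pass, report that the limit was not reached within 5-20%. If 5% fails, report that no unchanged load was shown.
5. If no margin can be justified, reword the objective to estimating the gait change at each load.

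The text change is short. The real cost is committing to a margin before data are seen and sizing the study for it. Under the assumptions of the last step of the working, that means 35 to 215 children for margins of 0.5 down to 0.2 SD, and more if several parameters or loads must pass together. A small study may be unable to declare any load unchanged.

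### The objective promises a backpack weight limit for the walk to school, but the procedure observes only the immediate gait response over short walkway passes

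*Protocol*

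**What the plan says.** The Study goals and objectives section has two parts. The main clause is a comparison of spatio-temporal gait parameters across five load conditions. The reason given for it is that the study can detect "the limit weight in the BPs in the kids to go to the school without change in their gait". Nothing there limits this to immediate effects.

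The Rationale & background information section describes the everyday exposure: two-thirds of children report daily backpack use when "walking an average of 14.55 km to and from school each week".

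The Methodology section (Procedure) describes the test:

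- It adopts a reliability-testing procedure that involved "repeating this walk three times and calculating the mean speed".
- On the walkway, "the children walk from a point two metres in front of the bar and stopp at a point two metres behind the last bar", and afterwards "they will be instructed to turn around and walk back to the starting point".
- The data used are restricted to the instrumented stretch: "Only steps in the sensor areas will be included in the analysis".
- The conditions are no backpack and loads of 5%, 10%, 15% and 20% of body weight.
- The only longer walk mentioned precedes measurement: "Prior to data collection, the children performed one familiarization trial for five minutes".

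The Follow-Up section puts all loads on one occasion, with an interval of unstated length between them. No section describes a prolonged loaded walk or a measurement taken after one.

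**The concern.** The limit in the objective is attached to a journey that children make carrying a pack, while the measurements come from the first moments after each load is put on. A load that leaves gait unchanged over a few short passes has been shown to do only that. Its effect after a kilometre or more is a different quantity, and the design never observes it.

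At stake is what the trial may conclude for children aged six to 12. The background already cites load recommendations as a percentage of body mass, so a reported limit would be read in the same terms and applied to school journeys. The analysis cannot repair this: a comparison of loads on short-walkway data holds no information on carrying time. The gap therefore lies in the objective and the procedure, both of which are protocol content.

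**Working it through.** The protocol gives no figure for carrying distance or time per load, so there is nothing to reproduce. The check compares the distance tested with the journey named in the background.

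**Inputs from the protocol:** 14.55 km per week; 2 m before and 2 m after the bars, so 4 m plus the bar length per pass; a walk repeated three times, with a walk back.

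**Inputs that have to be assumed:** bar length 3 to 10 m; 3 passes per load, or 6 if each return walk counts; speed 0.8 to 1.3 m/s (the protocol asks only for a slow, comfortable pace); 8 to 12 trips a week, central value 10.

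**School trip** = 14.55 km / trips per week
- 8 trips: 14.55 / 8 = 1.82 km
- 10 trips: 14.55 / 10 = 1.455 km
- 12 trips: 14.55 / 12 = 1.21 km
- Duration at 10 trips: 1,455 / 1.3 = 1,119 s (about 19 min) to 1,455 / 0.8 = 1,819 s (about 30 min)

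**Distance per load** = passes × (4 m + bar length), with the share of a 1,455 m trip in brackets

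| Bar (assumed) | One pass | 3 passes | 6 passes |
|---|---|---|---|
| 3 m | 7 m | 21 m (1.4%) | 42 m (2.9%) |
| 5 m | 9 m | 27 m (1.9%) | 54 m (3.7%) |
| 10 m | 14 m | 42 m (2.9%) | 84 m (5.8%) |

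A trip is thus 1,455 / 84 = 17 to 1,455 / 21 = 69 times as long as the test. Across 8 to 12 trips a week the share runs from 21 / 1,819 = 1.2% to 84 / 1,212.5 = 6.9%.

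**Walking time per load** = distance / speed: from 21 / 1.3 = 16 s to 84 / 0.8 = 105 s, about 0.3 to 1.75 minutes. Time spent standing with the pack on is not stated and is not included.

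**Does the unstated bar length matter?** For six passes to equal one trip, the bar would have to be 1,455 / 6 − 4 = 238.5 m. With the shortest trip it would be 1,212.5 / 6 − 4 = 198 m. The mismatch does not depend on the assumed length.

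**Does the familiarization trial close the gap?** It is a single trial before data collection and is not said to be loaded or repeated for each load. Even if five loaded minutes at 1.0 m/s (300 m) were credited to every load, the largest total would be 300 + 84 = 384 m, and 384 / 1,455 = 26% of a trip.

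**The case against.** The main clause of the objective, comparing gait across five loads, is exactly what the procedure delivers. The mention of school sits in a loosely worded subordinate clause and could be read as identifying school backpacks, with no whole journey intended. The 14.55 km figure comes from a cited source and is not set as an exposure to be tested. Short-walkway gait testing is a legitimate design choice.

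Much of this stands, and it limits the point to the claim: the comparison of loads needs no change. But the same sentence says that a limit for going to school can be detected, the background gives that setting a distance, and no other section narrows the conclusion.

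The detail of the test also has to be stated with care. The three repeats describe the adopted reliability procedure, and the five conditions come later without a number of passes for each. Three per load is a reasonable reading, not a stated fact. Nor can the exposure be fixed at the first minute, since the range above extends to 1.75 minutes.

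A reader might go further and infer that the study would set the limit too high, or that a load showing no change is an upper bound on any limit for the school walk. The protocol does not support either. It says nothing on whether gait effects grow, persist or fade with carrying time. If they build up, a load showing no change here could be too permissive. If children adapt to a new load, the test could flag a change that later disappears, and the error would run the other way.

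**Conclusion.** The point holds as a mismatch between the stated claim and what is observed. Each load is tested over about 21 to 84 m, against a school trip of about 1.2 to 1.8 km. The exact share rests on assumed bar length, passes, speed and trips per week; the conclusion does not, because only a bar of roughly 200 m or more would remove the gap. The design supports statements about the immediate gait response to each load in one session. It does not support a limit for the walk to school, and the direction of any error in such a limit cannot be determined from the protocol.

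**What to change.** In Study goals and objectives, and in any planned conclusion:

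- restate the aim as the immediate effect of each load on spatio-temporal gait parameters over a short walkway in one session;
- remove the journey to school as the setting for the limit;
- state that the result does not establish a limit for sustained carrying, without calling it an upper bound on such a limit.

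Stating the bar length and the number of passes per load in the Procedure would let readers see the exposure actually tested.

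This is a change of wording only. Data collection and the comparison of loads stay as they are. The price is a narrower claim.

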**Study Design**

An experimental, cross-sectional design will be conduct. We will examine schoolchildren between aged six to 12 years, at schools in the Spanish provinces of Malaga, from November 2018 to January 2019. The inclusion criteria will be: age between six and 12 years, no pain in the lower limb and back at the time of examination. The exclusion criteria will be: recent injury to the lower limb and back, alterations in the foot bones, congenital structural changes to the ankle, flatfoot associated with cerebral palsy, surgical treatment of foot or lower leg, or any genetic, neurologic or muscular conditions.

**Methodology**

### *Procedure*

### Two examiners will be responsible for the system software and collecting data. General information, including height and weight, will be recorded. To measure gait parameters, the protocol use for the Optogait reliability testing will be used^17^. This involved the children walking on a walkway at a comfortable speed, repeating this walk three times and calculating the mean speed. Prior to data collection, the children performed one familiarization trial for five minutes. Children will be asked to walk naturally, facing forward, with their hands out of pockets; wearing light, comfortable clothes, with the BP placed correctly. As the children start walking, the researchers selected the foot of the first step inside the bars, in the Optogait software. After being instructed to ‘*walk slowly at a comfortable speed’*, the children walk from a point two metres in front of the bar and stopp at a point two metres behind the last bar, to minimize effects of acceleration and deceleration . After this, they will be instructed to turn around and walk back to the starting point.. Only steps in the sensor areas will be included in the analysis. Recording six to eight strides is reported as sufficient to obtain representative data for unimpaired adults (defined as 95% confidence intervals within 5% of error)^27^. Subsequently, five experimental conditions will be measured: without BP, BP loads of 5%, 10%, 15%, and 20% of body weight. The order of these loaded conditions was random.

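### The spoken instruction asks for slow walking while the protocol otherwise wants natural, comfortable walking, and gait speed, though computed, is not a listed outcome

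*Protocol*

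**What the plan says.** All the pace wording is in the protocol, Methodology, Procedure, and it takes three forms:

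- The reliability-testing procedure that the study adopts: "This involved the children walking on a walkway at a comfortable speed", with "repeating this walk three times and calculating the mean speed".
- The general direction: "Children will be asked to walk naturally, facing forward".
- The instruction given to the child: "walk slowly at a comfortable speed".

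Each child is measured under five conditions: "without BP, BP loads of 5%, 10%, 15%, and 20% of body weight". On sequence, the section says "The order of these loaded conditions was random".

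Data Management and Statistical Analysis lists the gait parameters as "step length, stride length, single limb support time, double limb support time, swing and stance phase times". Neither speed nor cadence is among these six. The planned comparison is given as "The one-way analysis of variance (ANOVA) will be performed to compare the groups with Bonferroni post-hoc test".

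Study goals and objectives states the aim: to find the heaviest pack that children can carry to school with their gait unaltered.

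**The concern.** Slow is a different target from natural or comfortable. Children aged six to 12 would have to settle the conflict themselves. If they obey the word *slowly*, the unloaded reference walk is already slower than their everyday gait. The weight limit would then describe a walking condition that the objective does not ask about. A child who is already walking slowly on request may also have less scope to slow further when the pack gets heavier, so a response of direct interest could be muted.

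The second part is what happens to speed. The adopted procedure calculates it, but it is absent from the parameter list. If load makes children slow down, that is a change in gait and bears on the weight limit. The plan would show it only indirectly, as a shorter stride, longer phase times or both, and a reader could not see that one change of pace lies behind several reported changes.

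**Working it through.** **Figure to reproduce.** There is none. The protocol gives no sample size, effect size or standard deviation for the load comparison. Its only sample figure, 25 children, is for test-retest reproducibility.

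**Pace wording compared.** Two of the three descriptions (comfortable, natural) agree with each other and with the objective. The third adds *slowly*, and it is the one given as the instruction to the child.

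**Speed and the listed outcomes.** Let L be stride length and T = stance time + swing time. Then speed v = L / T. If v changes, L or T or both must change, and these are built from listed outcomes. The identity does not say how a change of pace divides among step length, single support and double support.

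**Illustrative size.** Assume that a share b of the log change in speed is taken up by stride length, with b from 0.4 to 0.6. For a proportional speed change δ:

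- L is multiplied by (1 + δ)^b
- T is multiplied by (1 + δ)^(b − 1)

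| Slowing | Stride length | Stride time |
|---|---|---|
| 2% | −0.8% to −1.2% | +0.8% to +1.2% |
| 5% | −2.0% to −3.0% | +2.1% to +3.1% |
| 10% | −4.1% to −6.1% | +4.3% to +6.5% |

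For example, at 5% slowing and b = 0.4, 0.95^0.4 = 0.980 (−2.0%) and 0.95^(−0.6) = 1.031 (+3.1%).

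**Could a pure change of pace reach significance in a listed outcome?** Assume a baseline stride of 1.10 m, a 5% slowing and b = 0.5. The stride then shortens by 1.10 × (1 − 0.95^0.5) = 0.0279 m. Five conditions give 10 pairwise contrasts, so Bonferroni α = 0.05/10 = 0.005 and z = 2.807. For a paired contrast, probability = Φ(0.0279 / (SD_diff/√n) − 2.807).

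| n (assumed) | SD_diff 0.08 m | SD_diff 0.04 m |
|---|---|---|
| 25 | 14% | 75% |
| 50 | 36% | 98% |
| 100 | 75% | about 100% |

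If the conditions were treated as independent groups, with an assumed between-child SD of 0.15 m, the same slowing would be significant with probability 2%, 3% and 7% at n = 25, 50 and 100. So slowing may appear as an unlabelled stride-length finding or go unnoticed, depending on inputs that the protocol does not give.

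**Can speed be recovered?** Yes, from each child's data. With 5% slowing, b = 0.5 and an assumed stride time of 1.0 s, L = 1.0721 m and T = 1.0260 s. Then L/T = 1.045 m/s, which is 0.95 × 1.10. From published group means a reader gets only an approximate ratio, with no standard error or test.

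**The case against.** A reader might go further and infer that a change of pace cannot be told from a load effect. The documents do not support that:

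- The objective asks about change in gait as such. Slowing caused by the pack is part of the total effect of load, not a confounder of it. Only an effect at constant speed is left unseparated, and the protocol does not claim to estimate one.
- No different wording is described for any load, and the loaded conditions are in random order. Ambiguous wording therefore mainly adds variability and limits reproducibility and relevance. It does not by itself bias the comparison between loads.
- Speed can be rebuilt from the listed outcomes if the phases are kept as times, so the gap is in what is tested and reported.

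A reader might also infer that speed drives all six outcomes. The protocol does not say so, and the identity binds only stride length and the sum of stance and swing times. Nor should the shifts above be set against the 5% error figure in Procedure. That figure is a precision criterion for how many strides to record in unimpaired adults, not a threshold for a meaningful load effect.

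It can fairly be added that the sentence on mean speed describes the cited reliability procedure, whose details are not visible here, and that supplementary models are commonly left to an analysis plan. Both are true. But the protocol says it will use that procedure, and the spoken instruction and the parameter list are both fixed in this document. Those two items stand.

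**Conclusion.** The point holds in limited form. The pace instruction is inconsistent, and the version given to the child moves the measurement away from ordinary walking. Gait speed is computed under the adopted procedure but is not a listed outcome, so slowing under load is neither tested nor reported directly. The inconsistency and the omission can be read from the text without assumptions. That slow walking leaves less room for further slowing is a plausible mechanism for which the protocol offers no data.

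The numerical size is illustrative only. It rests on the assumed amount of slowing, the 40 to 60% share, the baseline stride, the standard deviations and the sample sizes. No bias between loads and no altered conclusion is shown. This should be corrected, but it does not undermine the design.

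**What to change.** 1. In Procedure, delete *slowly* and give one scripted comfortable-speed instruction, identical in all five conditions. Bring the other pace wording in that section into line with it.
2. In Data Management and Statistical Analysis, add gait speed to the listed parameters and analyse it like the others.

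The cost is one word in the script and one further outcome from a quantity already calculated. The downside is more testing: with all 10 pairwise contrasts per outcome, the count rises from 6 × 10 = 60 to 7 × 10 = 70.

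A speed-adjusted model is optional. If used, label it as supporting only: speed lies on the causal path from load to gait, so adjusting for it answers a different question from the total effect of load.
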